## Abstract

Cohort studies using large-scale databases have become increasingly important in recent years. The Tokushukai Medical Group is a leading medical group in Japan that includes 71 general hospitals nationwide from Hokkaido to Okinawa, with a total of 18,000 beds, and a unified electronic medical record system. This retrospective cohort study aims to evaluate the real-world outcomes of systemic therapy for Japanese patients with cancer using this merit of scale. All adult patients with cancer who received systemic therapy using a centrally registered chemotherapy protocol system at 46 hospitals from April 2010 to March 2020 will be identified (~48,850 patients). Key exclusion criteria include active double cancer and inadequate data extraction. Data will be obtained through electronic medical records, diagnosis procedure combination data, medical prescription data, and the national cancer registration system that includes sociodemographic variables, diagnostic and laboratory tests, concomitant drug prescriptions, cost, and overall survival. Kaplan–Meier estimates will be calculated for time-to-event analyses. Stratified/conventional Cox proportional hazards regression analyses will be conducted to examine the relationships between overall survival and related factors. Our findings provide important insights for future research directions, policy initiatives, medical guidelines, and clinical decision-making.

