Details of hospitalization information such as diagnosis at admission (ICD-10), type of admission (scheduled or emergency), date of admission and discharge, outcome at discharge, complication (ICD-10), costs, and history of smoking (Brinkman index) can be extracted from the DPC data, which serves as the National Hospital Discharge Database for clinical studies in Japan [18,22].

Prescription data, such as the name and dose of the medicine, as well as the date and days of prescription, can be added from the electronic ordering system (e-Karte and Newtons2). The following treatment agents will be assessed in this study: (1) antitumor agents, (2) antihypertensive agents, (3) antithrombotic and antiplatelet agents, (4) antidiabetic agents, (5) antilipidemic agents, (6) antibacterial/antiviral/antifungal agents, (7) antiacid agents, (8) steroids, and (9) probiotics.

Furthermore, laboratory test information, such as blood cell count, biochemical tests, tumor markers, coagulation/fibrinogenic tests, infectious diseases, and urinalysis, can be retrieved from the electronic ordering system (e-Karte and Newtons2). The detailed parameters are listed in Table 2. Admission, prescription, and laboratory test data are combined with basic patient information with anonymized identification and cleaned again by Tokushukai Information System Inc. The final anonymized datasets, created as described above, will be handed over to statistical analysts with simplified case identification.

The analysis will be performed using statistical software (R, SAS, SPSS, or other statistical software) on computers of internal and external research institutes (Kobe University (Kobe, Japan) and deCult Co., Ltd. (Hatsukaichi, Japan)). Data will not be shared, except among computers that process and analyze them.

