### 2.4. Sample Size Calculation

The sample size for each cancer type is estimated based on the actual number of patients rather than specific hypotheses. Only 27 hospitals were equipped when the chemotherapy protocol system was started in April 2010, and the number of hospitals where this protocol system was used increased to 51 in March 2020. During this study period, the number of registered regimens increased rapidly, reflecting advances in oncology. These dynamic shifts preclude simple sample-size calculations. Alternatively, each sample size over the study period can be estimated based on the number of patients receiving drugs through the protocol system in 2019 (176 for biliary tract cancer, 1534 for breast cancer, 2324 for colorectal cancer, 212 for esophageal cancer, 956 for gastric cancer, 72 for kidney cancer, 1473 for lung cancer, 319 for ovarian cancer, 1026 for prostate cancer, 501 for pancreatic cancer, 71 for uterine body cancer, 83 for uterine cervix cancer, 199 for urinary tract cancer, 104 for gastrointestinal stromal tumors, and 123 for liver cancer). The expected sample sizes are listed in Table 3.

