### 2.5. Statistical Analysis

Basic statistics (absolute and relative frequencies for categorical variables; quartiles, maximum, minimum, and mean for continuous variables; and quartiles and relative frequencies for discrete variables) will be obtained to summarize the distribution of variables related to patient background factors, complications, other prognostic factors, and endpoints.

Kaplan–Meier curves will be obtained for each stratum consisting of patient background and prognostic factors for the occurrence of events associated with various endpoints (overall survival, time to treatment failure, recurrence-free survival, and adverse events). Several univariate logistic regression analyses will be performed, with the presence or absence of events in each stratum as the objective variable and the categorical value of each background or prognostic factor as the explanatory variable.

A hierarchical set of predictive models will be constructed by combining explanatory variables that are expected to contribute a single-layer or multi-layer proportional hazards model, which will be set up by incorporating each predictive model, and Cox multiple regression analysis will be performed. If proportional hazards are not acceptable, parametric hazard models such as the Cure–Weibull gamma-frailty model or the mixed Weibull gamma-frailty model will be applied for survival time analysis (including in combination with logistic regression models) [24]. Based on the likelihood (or partial likelihood in the case of Cox regression), the Akaike information criterion (AIC) and Bayesian information criterion (BIC) will be used to explore the optimal model (if the number of cases covered differs between models, the average AIC and BIC per case are used instead).

Regarding the estimated value of the regression coefficient of the explanatory variable included in the optimal model, if *p* value is <0.05, it will be judged as an important prognostic factor, and the 95% confidence interval of the hazard ratio regarding the magnitude of the contribution of that factor will be calculated.

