Biliary tract cancer	800
Breast cancer	10,000
Colorectal cancer	10,000
Esophageal cancer	1000
Gastric cancer	5000
Gastrointestinal stromal tumor	500
Kidney cancer	350
Liver cancer	500
Lung cancer	10,000
Ovarian cancer	1500
Prostate cancer	5000
Pancreatic cancer	2500
Uterine body cancer	350
Uterine cervix cancer	350
Urothelial cancer	1000

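### Section 2.5 selects the model by AIC/BIC from an open candidate set and reads its hazard ratios from the same data; in the smaller cohorts this will over-fit

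*Protocol article*

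**What the plan says.** Section 2.5 sets out one route from candidate variables to reported results:

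- Candidates: "A hierarchical set of predictive models will be constructed by combining explanatory variables that are expected to contribute". No list, number or upper limit follows.
- Selection: on the likelihood, or on the partial likelihood for Cox regression, "the Akaike information criterion (AIC) and Bayesian information criterion (BIC) will be used to explore the optimal model".
- Reporting: a coefficient in the chosen model whose p "value is <0.05, it will be judged as an important prognostic factor", with a 95% confidence interval for its hazard ratio.

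The pool of possible candidates is described in section 2.2, which names nine drug classes and says of the laboratory data that "The detailed parameters are listed in Table 2". Section 2.2 also lists demographics, body size, performance status, stage, pathology, complications and smoking.

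Cohort sizes are not tied to model size. Section 2.4 states: "The sample size for each cancer type is estimated based on the actual number of patients rather than specific hypotheses". Table 3 runs from "Kidney cancer 350" (the same figure for uterine body and uterine cervix cancer) to 10,000 for breast, colorectal and lung cancer. Section 2.5 makes no distinction between them.

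**The concern.** AIC and BIC charge for the number of parameters in each model. They do not charge for having searched many models and kept the best, and they leave the winner's coefficients unshrunk. When the search is wide and deaths are few, variables are kept partly because their estimates happen to be large in this sample. The selected model then fits its own data better than it would fit new patients, and its hazard ratios lie too far from 1.

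The article calls these models predictive, and the Abstract and Discussion offer the findings for guidelines and clinical decision-making. For the smaller cancers, readers would see prognostic effects and a quality of fit that do not reproduce elsewhere. The rule as written gives no sign of which cohorts are affected, because it treats 350 and 10,000 patients alike.

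**Working it through.** **Inputs from the article**

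- Table 3 sums to 48,850, which reproduces the Abstract's total. The smallest cohort is 350.
- Cohorts of 1,000 or fewer: 800 + 1,000 + 500 + 350 + 500 + 350 + 350 + 1,000 = 4,850 patients in eight of 15 cohorts.
- Table 2: 10 + 26 + 9 + 5 + 9 + 2 = 61 laboratory items (60 if the leukocyte fraction is read as a heading). With nine drug classes, 61 + 9 = 70, before any clinical variable.

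**Assumptions, because the article gives no figure**

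Deaths in 30%, 50% or 70% of patients; 15 or 70 candidates; eight true factors; Cox-Snell R² of 0.1, 0.2 or 0.3.

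**Deaths per candidate at 350 patients**

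- 70 candidates: 105/70 = 1.5, 175/70 = 2.5, 245/70 = 3.5.
- 15 candidates: 105/15 = 7.0, 175/15 = 11.7, 245/15 = 16.3.

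**Expected shrinkage of a full model without selection**

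S = 1 + p / (n ln(1 − R²/S)), with p parameters and n patients. Results for R² = 0.1 / 0.2 / 0.3:

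| n | p | S |
|---|---|---|
| 350 | 15 | 0.72 / 0.84 / 0.90 |
| 350 | 70 | 0.37 / 0.55 / 0.67 |
| 1,000 | 15 | 0.88 / 0.94 / 0.96 |
| 1,000 | 70 | 0.61 / 0.77 / 0.84 |
| 10,000 | 70 | 0.94 / 0.97 / 0.98 |

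Solved for n at S = 0.9: n = p / ((S − 1) ln(1 − R²/S)). For p = 15 and R² = 0.1 this is 15 / (0.1 × 0.1178) = 1,274. For R² = 0.2 and 0.3 it is 597 and 370. All three exceed 350.

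**Simulated selection at n = 350**

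Cox data with eight true factors and backward elimination by AIC or BIC. The calibration slope is taken in new patients; 1 is ideal, and below 1 means coefficients are too extreme.

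| Candidates | Deaths | AIC slope | BIC slope |
|---|---|---|---|
| 15 | 30% | 0.74 | 0.72 |
| 15 | 50% | 0.82 | 0.83 |
| 15 | 70% | 0.87 | 0.90 |
| 70 | 30% | 0.36 | 0.52 |
| 70 | 50% | 0.48 | 0.71 |
| 70 | 70% | 0.54 | 0.76 |

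A separate simulation used log hazard ratios of ±0.3 per SD, pairwise correlation 0.3, 3,000 new patients and 100 data sets per scenario (20 at n = 5,000). It agrees closely: 0.36 / 0.48 / 0.55 (AIC) and 0.53 / 0.69 / 0.78 (BIC) with 70 candidates, and 0.86 for both criteria with 15 candidates and 50% deaths. At 50% deaths it also gives:

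| n | Candidates | AIC: slope; C-index apparent to new | BIC: slope; C-index apparent to new |
|---|---|---|---|
| 350 | 15 | 0.86; 0.691 to 0.669 | 0.86; 0.684 to 0.663 |
| 350 | 70 | 0.48; 0.732 to 0.636 | 0.69; 0.699 to 0.650 |
| 1,000 | 70 | 0.80; 0.696 to 0.666 | 0.94; 0.685 to 0.676 |
| 5,000 | 70 | 0.96; 0.685 to 0.679 | 0.99; 0.682 to 0.681 |

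With 350 patients, 70 candidates, 50% deaths and no true factor at all, the AIC model shows an apparent C-index of 0.645 against 0.499 in new patients. For BIC the figures are 0.584 and 0.501.

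**The case against.** The strongest reply has five parts.

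1. **Seventy is what is collected, not what is searched.** This stands. Section 2.5 restricts candidates to variables thought likely to matter. Table 2 includes items such as PSA, which is no plausible candidate in uterine cancers, and overlapping blood counts. A reader might infer that all 70 enter the search, but the article does not say so, and the 70-candidate results are an upper scenario. The problem does not vanish with 15, and nothing in section 2.5 holds the list to 15.
2. **Backward elimination is not the stated procedure.** This also stands. A comparison of a few constructed models would carry less optimism. The article does not say how many models the hierarchical set holds, so the simulated sizes are indicative.
3. **The aim is prognostic factors, not individual risk.** The Introduction says so, and section 2.5 ends in hazard ratios. A reader might infer that survival predictions for single patients will be wrong at the bedside, but no section promises such predictions. What remains is overstatement of the hazard ratios and of the fit of models that the article itself calls predictive.
4. **Most patients are in large cohorts.** True: 4,850 / 48,850 is about 10%, and the three cohorts of 350 make up 1,050 / 48,850, about 2%. But results are to be reported by cancer type, so each small cohort stands alone.
5. **Validation may be in a fuller document.** Silence on validation in a condensed article is weak evidence and is not the ground of this point. The ground is the rule that section 2.5 does state: selection and reporting on the same data, with an open candidate set, at every cohort size.

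**Conclusion.** The point holds for the smaller cohorts. At 350 patients the selected model will be over-fitted even with a short list: a slope of about 0.7 to 0.9 with 15 candidates, and about 0.35 to 0.55 (AIC) or 0.5 to 0.8 (BIC) with 70. At 1,000 patients the effect is moderate with a long list under AIC (0.80) and small under BIC (0.94). At 5,000 or more it is negligible for fit and for the size of coefficients, so a claim about all 15 cohorts would go too far.

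The direction of the bias follows from the stated rule. Its size rests on assumed death fractions, effect sizes, candidate numbers and backward elimination, none of which the article gives. The validity of p values after selection is a related but separate matter, and shrinkage alone would not settle it. The change is worth making because it needs no new data, but it does not threaten the study as a whole.

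**What to change.** In section 2.5:

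- For cohorts of about 1,000 patients or fewer, fix a short candidate list in order of clinical importance, scaled to the observed number of deaths, before any modelling. Alternatively, fit a penalised Cox model.
- For every cohort, repeat the whole AIC/BIC selection in bootstrap samples. Report the optimism-corrected C-index and calibration slope beside the apparent ones.
- Wherever a model is presented as predictive, multiply its coefficients by the corrected slope.
- Keep leave-hospital-out validation for the large cohorts. With 46 hospitals, 350 patients give 350/46, about 8 per hospital, too few to judge calibration; 10,000 give 10,000/46, about 217.

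The cost is extra analysis time. The downside is that reported performance will look less favourable than the apparent figures.

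### Section 2.5 selects the optimal model by partial-likelihood AIC/BIC without requiring equal strata, so for the same covariates a stratified Cox model beats its unstratified counterpart even when the stratifier is unrelated to survival

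*Protocol article*

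**What the plan says.** Section 2.5 of the protocol article builds a hierarchy of predictive models and places them in "a single-layer or multi-layer proportional hazards model, which will be set up by incorporating each predictive model, and Cox multiple regression analysis will be performed". The abstract names the model types: "Stratified/conventional Cox proportional hazards regression analyses will be conducted to examine the relationships between overall survival and related factors". The selection rule in section 2.5 starts "Based on the likelihood (or partial likelihood in the case of Cox regression), the Akaike information criterion (AIC) and Bayesian information criterion (BIC", and these criteria "will be used to explore the optimal model".

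The only provision for models that are not directly comparable concerns the number of patients: "if the number of cases covered differs between models, the average AIC and BIC per case are used instead". No sentence requires the ranked models to share the same strata.

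Prognostic conclusions come from the selected model alone. The rule begins "Regarding the estimated value of the regression coefficient of the explanatory variable included in the optimal model"; a p value below 0.05 makes the variable an important prognostic factor, and a 95% confidence interval for its hazard ratio follows. Parametric models with frailty terms are held for the case where proportional hazards cannot be accepted.

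**The concern.** A Cox partial likelihood compares each patient who dies with the patients still at risk in the same stratum. Splitting the cohort shrinks every comparison set, so the partial likelihood rises for a purely mechanical reason. The stratum-specific baseline hazards that absorb the stratifier's effect are never counted as parameters, so AIC and BIC impose no penalty. Values from models with different strata are therefore not on a common scale.

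What is at stake is the list of prognostic factors for overall survival, the primary endpoint. A stratifier has no regression coefficient. If a candidate factor such as performance status, which the strengths section presents as a major prognostic consideration, is offered both as a covariate and as a stratifier, the criterion prefers the version that cannot report its hazard ratio. As the main protocol, the article would pass this rule on to each cancer-type sub-project.

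**Working it through.** **Inputs.** From the article: cohort sizes of 350 to 10,000 per cancer type (Table 3), 46 hospitals (section 2.1), and the selection rule (section 2.5). The article gives no number of events, so event rates below are assumptions. It also gives no figure for the AIC/BIC rule that could be reproduced. As a side check, the Table 3 rows add to 48,850, which matches the abstract.

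**Step 1: algebra.** Let patient i in stratum k die at time t, with risk set R, its stratum part R_k, and linear predictor η. The unstratified Cox term factorises:

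exp(η_i) / Σ_R exp(η) = [Σ_{R_k} exp(η) / Σ_R exp(η)] × [exp(η_i) / Σ_{R_k} exp(η)]

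The first bracket is at most 1 and the second is the stratified term. So at any coefficient values, and hence at the maximum, the stratified log partial likelihood is at least the unstratified one. If the stratifier was a covariate in the unstratified model, its coefficient cancels within strata, so the stratified model also saves a parameter. The same argument holds for any finer, nested stratification.

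**Step 2: size.** With K equal strata unrelated to survival, the first bracket is about 1/K. With d events, −2 log partial likelihood falls by about 2 × d × ln(K). For K = 2 this is 2 × 0.693 = 1.39 per event. With the same covariates the penalties are equal, so AIC and BIC fall by the same amount.

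**Step 3: simulation at Table 3 sizes.** Assumed: exponential survival with baseline hazard 0.3 per year, uniform censoring over 0.5 to 5 years, a 50/50 factor with hazard ratio 2.0, and about 64% events. There were 300 runs at n = 350 and n = 1,000, and 60 at n = 10,000.

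| n | Events d | 2 × d × ln 2 | Mean AIC fall, two coin-flip strata | Mean AIC fall, adding the real HR 2 factor |
|---|---|---|---|---|
| 350 | 223 | 309 | 307 | 24.6 |
| 1,000 | 637 | 883 | 880 | 71.5 |
| 10,000 | 6,354 | 8,809 | 8,807 | 747 |

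With no effect in the data, the coin-flip strata were preferred to no strata in 100% of runs at each size.

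**Step 4: second simulation under other assumptions.** Assumed: exponential survival and censoring, one normal covariate with log hazard ratio 0.4 per SD, a binary factor with hazard ratio 1 to 4, and about 76% to 84% events. There were 300, 200 and 20 runs per hazard ratio at the three sizes.

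- Adding two coin-flip strata to the same covariates won on both AIC and BIC in 100% of runs. With the factor at hazard ratio 1 the mean AIC falls were 364, 1,049 and 10,565. The formula gives 2 × 267 × 0.693 = 370, 2 × 761 × 0.693 = 1,055 and 2 × 7,626 × 0.693 = 10,570.
- Stratifying on the real factor instead of estimating it won in 100% of runs, even at hazard ratio 4 (mean AIC falls of 334, 961 and 9,634).
- At n = 1,000, random strata with K = 2, 4, 10 and 46 gave mean AIC falls of 1,047, 2,094, 3,452 and 5,639. The value 46 is the number of hospitals.
- A stratum of 3 patients out of 350, with the same covariates, won in 100 of 100 runs.

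**Step 5: per-case averaging.** It applies only when case numbers differ. With the same patients both criteria would be divided by the same n, so the order stays. At n = 1,000 the fall of 880 becomes 0.88 per patient, still in favour of the coin-flip strata.

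**Step 6: limits.** Five very unbalanced strata (96/1/1/1/1%) beat two balanced, non-nested strata in 0 of 100 runs. Coin-flip strata with the covariate omitted lost to the unstratified model containing it in all 50 runs once its log hazard ratio reached 2.0 per SD. A 5% stratum with the covariate omitted won only 10% of runs at 0.8 per SD.

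**The case against.** **The comparison across strata is not explicit.** Single- and multi-layer are not defined, the abstract says that both Cox types will be run but not that they will be ranked, and section 2.5 forms candidates by combining explanatory variables. It could describe covariate selection within one fixed stratification, where AIC and BIC are sound. This stands as a limit on certainty. Still, the abstract's pair is the natural meaning of single- and multi-layer, and section 2.5 gives one unrestricted rule.

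**Detail may be left to the full plan or the sub-projects.** How strata are defined may be. But the article states the selection rule and a comparability provision, and that provision does not reach this case.

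**Stronger readings that the documents do not support.**
- A reader might infer that more strata always win. That holds only for nested strata with the same other covariates; the reversals in step 6 show the rest.
- A reader might infer that noise strata displace true covariates. In simulation, a coin-stratified model omitting a factor with hazard ratio 2 or 4 did beat the unstratified model containing it in every run. But a full candidate set would also hold the coin-stratified model that keeps the factor. Within fixed strata AIC works normally, so a real covariate would be retained. Only the factor used as the stratifier loses its coefficient.
- A reader might infer that Cox partial likelihood will be ranked against full parametric likelihood. Section 2.5 makes the parametric models a fallback, which reads as sequential use.
- A reader might infer a search for ever finer or random strata. Nothing in the article says so; the coin flip here only illustrates a stratifier without information.

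**The stratifier does not vanish from the report.** Kaplan–Meier curves by stratum and univariate logistic regressions remain planned. What is lost is its adjusted hazard ratio and its p value, on which the judgement of importance rests.

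**Conclusion.** The point holds in a limited form. If section 2.5 is applied as written to a set containing stratified and unstratified Cox models, AIC and BIC cannot validly choose between them: each unstratified model is beaten by its own stratified counterpart, whether or not the stratifier matters. The direction is a mathematical result and does not depend on the assumed event rate. The size does depend on the number of events, and the formula assumes roughly equal strata unrelated to survival. In the first simulation the artefact for two strata is about twelve times the AIC gain from a real balanced factor with hazard ratio 2 (880 / 71.5 = 12.3 at n = 1,000).

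The consequence for the prognostic results requires that a candidate factor is among the possible stratifiers. The conclusion also rests on reading single- and multi-layer as the abstract's conventional and stratified models, which is likely but not stated.

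**What to change.** Add to section 2.5, or to the statistical analysis plan that implements it:

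1. AIC and BIC are compared only among models with identical strata, the same patients and the same type of likelihood (partial or full). The mechanical gain from stratifying then cancels.
2. Whether to stratify is decided separately and not by AIC or BIC, for example from proportional-hazards diagnostics or by prespecifying a nuisance stratifier such as hospital.
3. Factors whose prognostic importance is to be judged stay in the model as covariates, so that each has a hazard ratio and a p value.

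This costs a few sentences and needs no new data. The small downside is that no single AIC/BIC ranking across stratified, unstratified and parametric models will be available.

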### 2.2. Information Source and Data Collection

Information on the patients who met the inclusion criteria will be extracted by the Tokushukai Information System Inc., while researchers will be blinded to statistical analyses. Figure 1 provides an overview of how variables will be collected.

Patient demographic data, including age, birth year and month, sex, postal code, and insurance type, were documented at the time of the issuance of medical record identification. In addition, body height, body weight, body mass index, body surface area, and date of measurement were recorded based on practical requirements. Moreover, the date of the last visit, the last date of survival confirmation, the date of death, and the diagnosis on medical receipt were automatically recorded as part of routine clinical practice. The above information can be extracted from a unified medical record system (e-Karte and Newtons2, Software Service, Inc., Osaka, Japan).

Treatment information, including inpatient and outpatient therapies, particularly chemotherapy regimens, can be retrieved from a shared chemotherapy protocol system (SSI srvApmDrop, Software Service, Inc., Tokyo, Japan). This system links the start and end date, the date of administration, the treatment interval, the number of treatment cycles, the dose of administration, the data of dose adjustment, and the performance status.

Data from the Japanese National Cancer Registry [19,20] are available for all hospitals, including the diagnosis (date, site, laterality, pathology, and differentiation), staging (clinical and pathological TNM classification [21]), date of the first visit, treatment details (surgery, endoscopic treatment, radiotherapy, chemotherapy, and endocrine therapy), and survival outcomes (last date of survival confirmation, date of death, and cause of death).

Patient, treatment, and cancer registry data are combined with anonymized identification and cleaned by Tokushukai Information System Inc. (Osaka, Japan). Patients with double cancer and/or diagnostic errors will be excluded from the study. Treatment history will be organized, and missing data will be supplemented by a direct check of medical records in cases of inconsistency or lack of information. Patients with unknown treatment history will be also excluded.

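### Ranking Cox models fitted to different numbers of patients by average AIC or BIC per case is invalid: the criterion falls as patients are dropped, whatever the covariate

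*Protocol article*

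**What the plan says.** Section 2.5 plans a hierarchical set of predictive models for the endpoints, and "Cox multiple regression analysis will be performed". Parametric models are a fallback: "If proportional hazards are not acceptable, parametric hazard models such as the Cure–Weibull gamma-frailty model" and similar models come in at that point. For selection, "the Akaike information criterion (AIC) and Bayesian information criterion (BIC) will be used to explore the optimal model", and the basis is stated as "Based on the likelihood (or partial likelihood in the case of Cox regression". When the candidate models do not cover the same patients, the rule is: "if the number of cases covered differs between models, the average AIC and BIC per case are used instead". A factor with p < 0.05 in the chosen model is then treated as established: "it will be judged as an important prognostic factor".

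On incomplete data, section 2.2 says that "missing data will be supplemented by a direct check of medical records in cases of inconsistency or lack of information", and Table 1 excludes patients whose data extraction is inadequate. Neither place requires the models being compared to be fitted to the same patients, and the per-case rule itself expects that they may not be.

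**The concern.** Differences in AIC or BIC have their usual meaning only between models fitted to the same patients. Dividing by the number of cases looks like a correction for unequal numbers, but it does not work for the partial likelihood that the plan names for Cox regression. Risk sets shrink when patients drop out of a model, and the criterion per case shrinks with them. A candidate model that contains an incompletely recorded covariate therefore receives credit for the missing records themselves.

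Prognostic factors for overall survival are a stated aim of the study (Introduction), and the selected model decides which factors are tested. A rule that favours incomplete covariates can choose the wrong model and reduce the number of patients behind the reported hazard ratios.

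**Working it through.** The plan gives no figure for this rule, so there is nothing to reproduce.

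**Inputs from the documents.** The selection rule and the partial-likelihood basis (section 2.5); cohort sizes from 350 to 10,000 (Table 3).

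**Assumed inputs, not in the documents.** A binary factor with 50% prevalence; HR 1.5, 2 or 3; event fraction 0.62 to 0.78; 0 to 30% missing.

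**Step 1: the built-in reward.** For a Cox model without covariate effects, −2 log partial likelihood = 2·Σ ln(risk-set size), summed over events. Per case this is about 2·d·ln(n) plus a constant, so dividing by n leaves a term that still grows with n. Dropping a random fraction m multiplies each risk set by about (1−m) and leaves d unchanged. The criterion per case falls by

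2·d·ln(1/(1−m)).

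With d = 0.69 this is 0.07, 0.15, 0.31 and 0.49 for m = 5%, 10%, 20% and 30%. The covariate does not enter the formula.

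**Step 2: what a real factor earns.** A 50:50 factor improves −2 log likelihood by about 0.25·ln(HR)² per event. For HR 2 that is 0.25 × 0.693² = 0.120 per event, or 0.120 × 0.69 = 0.083 per case. The reward for 10% missing data (0.15) already exceeds it. Equating the two gives a break-even missing fraction of 1 − exp(−ln(HR)²/8): about 2% for HR 1.5, 6% for HR 2 and 14% for HR 3.

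**Step 3: simulation against the formula.** At n = 1,000, HR 2 and 66% events, the mean difference in AIC per case (noise model minus true-factor model) moved from +0.078 with nothing missing to −0.217 at 20% missing, a shift of 0.295. The formula gives 2 × 0.66 × ln(1/0.8) = 0.295.

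**Step 4: how often noise wins.** Noise-only Cox model against true-factor-only Cox model, HR 2, noise covariate missing completely at random, compared on AIC per case:

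| Cohort size | 5% missing | 10% missing | 20% missing |
|---|---|---|---|
| 350 and 1,000 | 40–47% | 80–88% | 96–100% |
| 5,000 (30 runs only) | 60% | 93% | 100% |
| 10,000 | 33–38% | 98–100% | 100% |

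The 60% rests on 30 runs close to break-even and should not be read more finely than that. At n = 1,000 the shares at 5%, 10% and 20% missing are 79%, 98% and 100% for HR 1.5, and 0%, 26% and 93% for HR 3. BIC per case gave nearly the same results. With both models fitted to the same patients, noise won in under 1% of runs for HR 2, and in at most 5% in the hardest setting (HR 1.5, n = 350).

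**Step 5: nested models.** True factor plus noise against true factor alone, n = 350, about 74% events. The larger model was wrongly preferred in 86–99.5% of runs at 5–20% missing. The penalty cannot prevent this: one extra parameter costs about 2/350 = 0.006 per case in AIC, or ln(350)/350 = 0.017 in BIC, while 5% missing already earns 2 × 0.74 × ln(1/0.95) = 0.076. The true factor nevertheless stayed significant in 99–100% of runs, and the noise term reached p < 0.05 in 4–6%, about the nominal rate.

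**Step 6: full likelihood.** Weibull models at n = 1,000 with data missing completely at random: the mean difference for HR 2 stayed at +0.074 to +0.079 and noise won in 0–1% of runs (3–15% for HR 1.5). With 30% missing, concentrated in good-prognosis patients, noise won in 65% (HR 2) and 75% (HR 1.5). With 30% missing, concentrated in poor-prognosis patients, the HR 2 difference moved the other way, to +0.160.

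**The case against.** Four points can be made for the plan.

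- **Second gate.** A factor is called important only if p < 0.05 in the chosen model. In the noise-only contest, noise both won and reached p < 0.05 in only 3–4.5% of runs, and in nested comparisons the true factor survives. This stands. A reader might infer that missingness, rather than prognostic value, decides which factors are declared prognostic. The documents do not support that: a true factor is lost only when the winning candidate model omits it.
- **Cox against parametric.** Section 2.5 names both likelihood types in one sentence, and a reader might infer that a Cox AIC will be ranked against a Weibull AIC. Those scales do differ: changing months to days shifts a parametric AIC by 2·ln(30.44) = 6.83 per event and leaves the Cox AIC unchanged. But the text makes the parametric models a fallback after the proportional-hazards assessment and nowhere says the families are ranked together.
- **Full likelihood.** It would be too broad to say that dividing by n fails for every likelihood. The automatic reward belongs to the Cox partial likelihood (step 6).
- **Extent of missing data.** The documents give no missing fraction for any covariate and do not say that laboratory tests were done only on indication. Chart checks and exclusions will reduce unequal numbers. They do not remove them: section 2.2 says body measurements were taken as practice required, smoking history comes from inpatient claims data (section 2.2 and Introduction), and the Strengths and Weaknesses section says genetic mutations mostly need direct chart access.

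The step is also exploratory, and it does not touch the Kaplan–Meier estimates, the endpoints or eligibility. That limits the severity but does not make the rule valid.

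**Conclusion.** The per-case rule is wrong as written for Cox regression, the main planned model, and should be fixed. The bias is systematic even when data are missing completely at random, applies to AIC and BIC alike, and is not cured by a larger cohort. Its direction and formula follow from the partial likelihood; how often it changes the choice rests on the assumed hazard ratio, prevalence, event fraction and missing fraction. For a factor with HR 2, about 6% missing in a competing covariate is enough to tip the comparison.

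The practical harm depends on the comparison. Between nested models it is superfluous terms and fewer patients. Between non-nested models it can be the loss of a true factor. For the parametric fallback the rule misleads mainly when missingness is related to prognosis, and then in either direction. This is a stated rule rather than a detail left to a later document; an analysis plan that followed section 2.5 would carry the error forward.

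**What to change.** In section 2.5, delete the parenthesis on average AIC and BIC per case. State instead that, within each sub-project, AIC and BIC are compared only between models of the same likelihood type fitted to one common set of patients. That set can be the patients complete on all candidate covariates, fixed before models are compared, or the same multiply imputed data sets for every model. The restriction to one likelihood type also rules out any ranking of Cox against parametric models.

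The cost is a short rewording plus either some patients lost to the common complete-case set or routine imputation work. No new data are needed.
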